### Sample size determination

5.3

The sample size for the quantitative primary endpoint “degree of satisfaction and levels of self‐perceived health‐related quality of life of patients” has been calculated in terms of standardized differences through Cohen's delta. Assuming a significance level of 2.5%, given that the endpoint is composed of two different questionnaires (EuroQol‐5D‐5L [EQ‐5D‐5L] and Catheter‐related quality of life questionnaires), and expecting large differences (0.95) between groups, a sample size of 25 per group would be enough, taking into account a dropout rate of 5%.

Regarding the qualitative primary endpoint, it is expected to reach information saturation with a maximum of four discussion groups composed of between 8 and 10 participants (a total of a maximum of 40 subjects), so the calculated sample size is considered sufficient.

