### Methods of data collection

5.4

The source and timing of measures are summarized in Table 1. In accordance with the proposed research objectives, the outcome measures that will be performed are the following.

**TABLE 1 bco2313-tbl-0001:** Source and timing of variables obtained for the study.

Variable	Method of obtention	Data collection format	Source	Timing			
				Baseline	4 weeks	Up 6 months AFUV	Close‐out
Baseline data (sociodemographic, clinical, and life habits)	Personal interview/PCDN	Paper/electronic	P and HP	X			
Magnitude of infection	Urine culture/PCDN	Paper/electronic	Microbiology laboratory	X	X		
Rate of infection (asymptomatic and symptomatic UTI)	Urine culture/PCDN	Paper/electronic	Microbiology laboratory	X	X		
Adverse events during catheter insertion	Observation/PCDN	Paper/electronic	HP	X			
Adverse events during catheterization time	ID/PCDN	Paper/electronic	P		X		
Catheter biofilm	Viable cells counting/PCDN	Paper/electronic	Microbiology laboratory		X		
Antibiotic treatments related to catheterization	ID/PCDN	Paper/electronic	P and HP		X		
Healthcare resources utilization	ID/PCDN	Paper/electronic	P and HP		X		
Quantitative data for QoL and catheter satisfaction	Patients' questionnaire and EuroQoL 5D questionnaire	Paper/electronic	P	X	X		
Qualitative findings for acceptability and experience	Discussion groups	Audio recording	P			X	
Catheter opinion (professionals)	Professional questionnaire	Paper/electronic	HP				X
Workload perceived	NASA‐TLX questionnaire	Paper/electronic	HP				X

Abbreviations: AFUV, after follow‐up visit; EuroQoL 5D, EuroQol questionnaire—five dimensions—five levels; HP, health professional; ID, incident diary; NASA‐TLX, NASA Task Load Index questionnaire; P, participant/relative, friend, or informal carer‐completed questionnaire; PCDN, Patient Clinical Data Notebook; QoL, quality of life perceived; UTI, urinary tract infections.

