##### Self‐perceived health‐related quality of life

The following instruments are administered to patients:
EQ‐5D‐5L^27^: This is a generic health‐related quality of life questionnaire that evaluates five domains: mobility, self‐care, usual activity, pain/discomfort, and anxiety/depression. Each domain is scored on a 5‐point scale, which yields a descriptive system that can be combined into a five‐digit number reporting the patient's state of health. Each EQ‐5D‐5L health state can be converted to a single summary index by applying a formula that attaches weights to each level in each dimension. A number of formulae or value sets are available for different countries, based on the valuation of EQ‐5D health states from general population samples. In this study, the value set estimated for Spain by Ramos‐Goñi et al.^28^ will be used. After applying these weights, the range of the summary index is 1 (perfect health) to 0 (health state equivalent to death). Negative values represent health states considered to be worse than death. The questionnaire also includes a visual analogue scale where responders are asked to indicate their health status on the day of the interview, ranging from 0 (worst possible health) to 100 (best possible health).Catheter‐related quality of life questionnaire: To evaluate the specific health‐related quality of life for long‐term catheterized patients, Rethink Medical has developed two specific instruments created in the context of this project based on the experience of our previous studies (Patient's workshop).^25^ The first one (Data S5), administered during the initial visit, consists of 47 questions, related to the patient's experience and journey with catheterization before the study, as baseline data. The questions are related to the type of catheter and accessories used, the experience of catheterization, emotions felt at the beginning (right from the moment of the prescription), satisfaction and comfort with the catheter, complications associated with catheter use, usability and complications associated with accessories and changes in the personal habits caused by the catheter's use, and how these issues have affected their lives. The second one (Data S6), administered during the follow‐up visit, consists of the same questions as the first one (but referred to the catheter and accessories used during the study) plus four questions related to information received when catheterized for the first time (total 51 questions). In order to quantitatively evaluate the answers, statements will include single answers with scores on a scale from 0 to 10, 0 to 5, and 0 to 4 for both questionnaires. The questionnaire devised by Rethink Medical is expected to be validated during the clinical study in conjunction with another study specially designed for its validation.

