### Analysis plan

5.7

A statistical analysis plan will document the scheduled analysis, to be finalized before the data lock. The final analysis will take place after full recruitment and follow‐up, at the end of the study.

The analysis population will consist of all patients who meet the selection criteria and are randomized. All patients included in the study and excluded from the analysis will be listed along with their reason for exclusion. Additionally, additional analysis will be performed on patients who complete 4 weeks with the catheter. Subjects who withdraw from the study for any reason after signing the informed consent will not be replaced. No imputation will be made for missing data.

Descriptive statistics will be carried out on the variables under study, using frequencies and percentages for qualitative variables and mean with standard deviation for quantitative variables that follow a normal distribution; otherwise, the median and interquartile ranges will be calculated.

A bivariate analysis will be carried out between the control–study groups with respect to the independent variables to know the comparability of the groups using the Chi square tests for qualitative variables and for the quantitative variables *t*‐Student or Mann–Whitney U, depending on the normality of the sample. All are under a 95% confidence interval and considering statistically significant results with a *p*‐value < 0.005.

In the event that the results are discordant, deviations and/or violations of the protocol will be analysed. For all analyses, the SPSS 24.0 statistical package^31^ will be used and will be carried out by a person who will not know if the patients have been in the intervention or control group.

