#### Cost‐effectiveness analysis

5.7.1

An economic evaluation of T‐Control versus the conventional Foley catheter from the public healthcare services perspective will be performed according to the analytical methods accepted by the scientific community.^32^ The cost‐effectiveness measure will be the incremental cost per quality‐adjusted life year (QALY) gained. QALYs are a generic health measure that combines information on life expectancy with the patient's quality of life. QALYs will be calculated based on the health‐related quality of life data collected according to the EQ‐5D‐5L instrument which will be collected for each patient. The time horizon will be the study duration. Costs included in the analysis will be those incurred by the public healthcare service. Unit costs will be obtained from the hospital centres accounting records whenever possible, from the eHealth cost database (Oblikue Consulting), and from national public sources. The mean total cost of each intervention evaluated will be presented using basic descriptive statistics (means, medians, and measures of variability such as variance).

Cost‐effectiveness will be calculated as the incremental cost‐effectiveness ratio which results from dividing the difference in costs between interventions by the difference in effects observed (QALYs). Nonparametric methods based on bootstrapped simulations will be used to calculate the confidence intervals around the incremental cost‐effectiveness ratio. In addition, the same nonparametric methods will be used to construct a cost‐effectiveness acceptability curve that will reveal the probability that each alternative is cost‐effective for different cost‐effectiveness thresholds (willingness to pay for an additional unit of effectiveness). Finally, deterministic sensitivity analysis (one‐way, two‐way, and multiway) will be performed with the aim of analysing the impact of the parameters on the cost‐effectiveness results. The analysis will be performed using the software R and the statistical package STATA (StataCorp LLC, College Station, USA).

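### EQ-5D-5L and the catheter questionnaire are measured at baseline, but the article names no baseline-adjusted estimate for the 4-week comparison or the QALY difference, which costs precision in a 50-patient trial

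*Protocol article*

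**What the plan says.** Protocol article, Table 1 (section 5.4): the row "Quantitative data for QoL and catheter satisfaction" is marked at baseline and at 4 weeks. Section 5.4.1 presents the first catheter questionnaire (47 questions) as baseline data. The follow-up version "consists of the same questions as the first one (but referred to the catheter and accessories used during the study"), plus four more questions.

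Section 5.3 sizes the trial on a standardised difference: "Assuming a significance level of 2.5%, given that the endpoint is composed of two different questionnaires", and "expecting large differences (0.95) between groups". It concludes that "a sample size of 25 per group would be enough", allowing for 5% dropout. No baseline correlation enters.

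Section 5.7 describes a bivariate comparison of the arms "with respect to the independent variables to know the comparability of the groups using the Chi square tests for qualitative variables", with Student's t or Mann-Whitney for quantitative variables according to normality. It names no ANCOVA, change score or other adjusted analysis. It also says that a statistical analysis plan, to be completed before data lock, will document the analysis.

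Section 5.7.1 divides the cost difference by the observed QALY difference over the study period. "Nonparametric methods based on bootstrapped simulations will be used to calculate the confidence intervals around the incremental" cost-effectiveness ratio, and the same methods produce an acceptability curve. Adjustment for baseline utility is not mentioned.

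**The concern.** In a trial of 25 per arm, chance can leave the arms noticeably different at baseline. Section 2.3 states no stratification, and the Discussion acknowledges a mixed population of men and women catheterised for different reasons. A baseline measurement of the same outcome is usually the best available covariate, and this trial already collects it.

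The article uses baseline variables only to test comparability. Under randomisation any imbalance is due to chance, so such a test answers no useful question and corrects nothing. If the same tests are applied to the outcomes, the normality check lets the data decide whether means or ranks are compared, whereas the sample size assumes a difference in means.

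The QALY comparison is the more exposed. With two utility measurements and an area-under-the-curve QALY, baseline and 4-week utility carry equal weight. A chance baseline gap therefore counts as much as a treatment effect of the same size at 4 weeks.

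**Working it through.** **Inputs from the article.** Standardised difference d = 0.95; alpha 2.5% (sidedness not stated, two-sided assumed); 25 per arm; 5% dropout, so 25 × 0.95 = 23.75, about 24 completers per arm; horizon about 28 days. **Assumed.** Power of 80% behind the sample size (not stated); baseline-to-week-4 correlation r (not given), taken over a range.

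**1. The article's own figure.**
- Normal approximation: n = 2 × (2.241 + 0.842)² / 0.95² = 21.1, so 22 per arm, and 22 / 0.95 gives 24.
- Exact two-sided t-test: 23 per arm, and 23 / 0.95 = 24.2 gives 25.

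The stated 25 is reproduced without any baseline adjustment. Since power is not stated, this is not the only possible reading: 90% power at one-sided 2.5% gives 26 or 27.

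**2. Power with adjustment.** ANCOVA multiplies the outcome variance by 1 − r², so the effective standardised difference is 0.95 / √(1 − r²). Noncentral t, 24 per arm, two-sided alpha 2.5%:

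| Analysis | Variance factor | Power | 48 completers are worth |
|---|---|---|---|
| Unadjusted | 1.00 | 83.1% | 48 |
| ANCOVA, r = 0.3 | 0.91 | 86.7% | 53 |
| ANCOVA, r = 0.5 | 0.75 | 92.7% | 64 |
| ANCOVA, r = 0.7 | 0.51 | 98.7% | 94 |

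The difference detectable with 80% power (normal approximation) falls from 0.89 SD to 0.85, 0.77 and 0.64 SD.

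**3. Chance imbalance.** The baseline difference between arms has standard error √(2/24) = 0.289 SD. It exceeds 0.3 SD in 30% of randomisations and 0.5 SD in 8%. An imbalance of x shifts the unadjusted 4-week difference by r·x. At x = 0.5 SD the shift is 0.25 SD (r = 0.5) or 0.35 SD (r = 0.7), and the type I error conditional on that imbalance is 5.6% or 7.5% against 2.5%. At x = 0.3 SD it is 2.4% or 1.7%, so inflation is confined to the larger imbalances. Averaged over randomisations it stays at 2.5%.

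**4. QALYs.** Assume area under the curve from two utilities over T = 28 days, with standard deviation s at each visit and 24 per arm.
- Effect: 0.5·d·s·T.
- Unadjusted SE: s·√((1 + r)/2)·T·√(2/24).
- SE adjusted for baseline utility: 0.5·s·√(1 − r²)·T·√(2/24).

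s and T cancel in effect/SE. The chance that a 95% interval spans zero is Φ(1.96 − effect/SE) − Φ(−1.96 − effect/SE):

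| d | r | Effect/SE unadjusted | Spans zero | Effect/SE adjusted | Spans zero |
|---|---|---|---|---|---|
| 0.95 | 0.3 | 0.475/0.233 = 2.04 | 47% | 0.475/0.138 = 3.45 | 7% |
| 0.95 | 0.6 | 0.475/0.258 = 1.84 | 55% | 0.475/0.115 = 4.11 | 2% |
| 0.5 | 0.3 | 0.250/0.233 = 1.07 | 81% | 0.250/0.138 = 1.82 | 56% |
| 0.5 | 0.6 | 0.250/0.258 = 0.97 | 84% | 0.250/0.115 = 2.17 | 42% |

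In absolute terms, a baseline utility gap of 0.05 alone adds 0.05/2 × 28/365 = 0.0019 QALY unrelated to treatment.

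**The case against.** Much of the case on the other side stands, and it limits the point.

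- **The analysis plan may already adjust.** Section 5.7 defers the scheduled analysis to a document that is not shown, and choosing covariates there is normal practice. Nothing in the article excludes adjustment. The point is therefore a method that the named ones should give way to, not a missing detail.
- **The primary test is not fixed.** A reader might infer that section 5.7 commits the trial to an unadjusted 4-week test. The sentence is tied to comparability of the groups and does not clearly cover the outcome. The normality-check complaint applies to the primary endpoint only if it does.
- **QALYs do not ignore baseline.** A reader might infer this from section 5.7.1. It uses the EQ-5D-5L data collected for each patient, which include the baseline visit. What is absent is adjustment for baseline utility.
- **The unadjusted comparison is neither invalid nor underpowered.** Its type I error holds under randomisation, and 25 per arm reproduces without adjustment if 80% power was intended. The trial also calls itself a pilot.
- **A QALY interval spanning zero does not leave the economic analysis without a result.** It makes an interval for the ratio hard to interpret, but the planned acceptability curve remains usable.
- **The catheter questionnaire is a weaker covariate.** Its baseline answers concern the previous catheter, its items use three different scales, no total score is stated, and it is not yet validated. Its correlation with the 4-week score is unknown.

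None of this removes the gain for EQ-5D-5L and QALYs, nor does it give the baseline significance tests a purpose.

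**Conclusion.** The point holds as a loss of precision and an exposure to chance imbalance, not as an error that invalidates the analysis. At the article's own design values, adjustment raises power from 83% to between 87% and 99%, and it cuts the share of trials whose QALY interval spans zero from about half to between 7% and 2%. With a smaller effect (d = 0.5) the adjusted share is still 42% to 56%, so adjustment helps the QALY comparison without rescuing it.

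These figures rest on assumed correlations (0.3 to 0.7 for power, 0.3 to 0.6 for QALYs), two-sided alpha of 2.5%, 24 completers per arm and an area-under-the-curve QALY. The case is firm for EQ-5D-5L and for QALYs. For the catheter questionnaire it depends on a score that has yet to be defined. The change is worth making because it is nearly free and the analysis plan is still to be finalised according to the article.

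**What to change.** In the analysis plan, before data lock:

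1. State the 4-week EQ-5D-5L comparison as an ANCOVA of the 4-week score on arm and baseline score, with robust or bootstrap standard errors in place of the normality check.
2. Define a score over the 47 items common to both catheter questionnaires, then analyse it in the same way.
3. Drop the significance tests of baseline comparability and describe the baseline data by arm.
4. Estimate incremental QALYs by regression on arm and baseline utility within each bootstrap sample, and keep the planned acceptability curve.

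Adding sex as a covariate and reporting incremental net monetary benefit beside the ratio are optional. If the plan already specifies items 1 and 4, only the article's wording needs to be brought into line.

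The cost is some wording and a few lines of code for EQ-5D-5L and QALYs. The catheter questionnaire also needs a scoring rule, which takes more thought. No extra data or patient burden is involved.

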### Random assignment

2.3

Participants will be assigned 1:1 to one of the two trial arms of the quantitative study by a local research team member using a centralized computerized randomization system (RAND2 software, The MathWorks Inc, Natick, USA, administered by the data management team, depending on the contract research organization [CRO]).

The blinded allocation sequence is concealed by the use of a centralized computerized randomization system. The personnel responsible for catheter insertion will enrol subjects on the randomization system.

The patient's identifying number will be consecutively assigned, and inclusion in the intervention group or control group will be carried out through the randomized numerical distribution generated by a random online generator.

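### The analysis plan's only significance threshold (p < 0.005, beside 95% intervals) does not match the 2.5% per questionnaire on which the sample size rests

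*Protocol article*

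**What the plan says.** Section 5.3 (Sample size determination) sets the level for the quantitative primary endpoint: "Assuming a significance level of 2.5%, given that the endpoint is composed of two different questionnaires", the two being the EQ-5D-5L and the catheter-related quality of life questionnaire. It continues with "expecting large differences (0.95) between groups" on the Cohen scale and concludes that "a sample size of 25 per group would be enough", "taking into account a dropout rate of 5"%. Power and sidedness are not given. Section 2.3 (Random assignment) fixes equal allocation: "Participants will be assigned 1:1 to one of the two trial arms".

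Section 5.7 (Analysis plan) describes bivariate comparisons of the two groups by chi-square, Student's t or Mann–Whitney U. It closes that paragraph with "All are under a 95% confidence interval and considering statistically significant results with a" p-value below 0.005. No other significance threshold appears in the section, and the 2.5% of section 5.3 is not mentioned there.

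**The concern.** The two sections give different levels for what appears to be the same decision: 0.025 per questionnaire in the design and 0.005 in the analysis. A primary comparison with p between 0.005 and 0.025 would succeed under section 5.3 and fail under section 5.7. The 95% interval beside the threshold adds doubt about what was meant, since it corresponds to a two-sided 0.05.

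The threshold bears on whether the quantitative primary endpoint is called positive. The article says that the statistical analysis plan is to be finalized before data lock. If the level stays open until then, it is chosen late in an open-label trial whose quantitative primary outcomes are patient-reported.

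**Working it through.** **Inputs.** From section 5.3: standardized difference d = 0.95, level 0.025 per questionnaire, 25 per group, dropout 5%. From section 2.3: 1:1 allocation. From section 5.7: threshold 0.005, 95% intervals, t test or Mann–Whitney U. Assumed because not stated: two-sided t test and 80% design power; one-sided testing and the normal approximation are shown as variants.

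**Step 1: reproduce the plan's sample size.** For a two-sample t test with n per arm, the degrees of freedom are 2n − 2 and the noncentrality is d·√(n/2). Power is the probability that the noncentral t exceeds the two-sided critical value in absolute size.

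- At 0.025 two-sided, n = 22 gives 79.2% and n = 23 gives 81.3%, so 23 evaluable per arm are needed for 80%.
- Allowing for dropout: 23 / 0.95 = 24.2, rounded up to **25**, the stated figure.
- At 0.005 two-sided, n = 31 gives 79.1% and n = 32 gives 80.8%, so 32 evaluable are needed; 32 / 0.95 = 33.7, or 34 per arm.

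The 25 per group therefore fits a two-sided 2.5% design at 80% power. It does not come from a two-sided 0.005.

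**Step 2: power at each level with the planned numbers.** Evaluable per arm: 25 × 0.95 = 23.75, taken as 24. Noncentrality: 0.95 × √12 = 3.29, with 46 degrees of freedom.

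| Method, 24 per arm | 0.025 | 0.005 | Loss (points) |
|---|---|---|---|
| t test, two-sided | 83.1% | 63.4% | 19.7 |
| Normal approximation, two-sided | 85.3% | 68.6% | 16.7 |
| t test, one-sided | 89.6% | 72.4% | 17.2 |

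With 23 evaluable per arm the two-sided t test gives 81.3% and 60.7%, a loss of 20.6 points. Across these variants the loss is about 17 to 21 points.

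**Step 3: the observed effects in dispute.** With 24 per arm, the smallest observed standardized difference that reaches significance is the critical t divided by √12. At 0.025 two-sided it is 2.317 / 3.464 = 0.67. At 0.005 it is 2.949 / 3.464 = 0.85. An observed difference between 0.67 and 0.85 would be positive under one section and negative under the other.

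**Step 4: if 0.005 was meant to be 0.05.** Two-sided t-test power with 24 per arm is 89.6% for each questionnaire. With both questionnaires tested at 0.05, the family-wise error is 1 − 0.95² = 9.75% if the tests are independent. The general bound is 0.05 + 0.05 = 10%. Positive correlation, which is likely for two quality-of-life instruments in the same patients, puts it below 9.75%. The split in section 5.3 implies 2 × 0.025 = 5%.

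**The case against.** The strongest objection is scope. The paragraph that ends with the threshold announces a comparison of the groups to judge their comparability, so the 0.005 could concern baseline tests alone. The wording does allow this, and a reader should not infer that section 5.7 explicitly fixes 0.005 as the primary decision rule. But the sentence opens by covering everything, and no other threshold is given for outcomes. The ambiguity is itself in need of repair.

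Second, 0.005 may be a typing slip for 0.05, as the 95% interval beside it suggests. A reader might infer that the trial has simply lost 20 points of power. The document does not support that as a flat statement, because under the slip reading power rises. The mismatch with section 5.3 nevertheless remains, now as a multiplicity problem.

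Third, one might count three incompatible decision levels. That goes too far: a 95% interval is an estimation convention, and reporting it beside a stricter test threshold is not in itself a contradiction. The firm conflict is between 0.025 and 0.005.

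Finally, this is a pilot, and the statistical analysis plan, which is not shown, may settle the level. That lowers the stakes, but the point is not an omission: the article prints two levels that disagree, after calculating a formal sample size with a level adjusted for two questionnaires.

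**Conclusion.** The point holds as an unreconciled conflict between sections 5.3 and 5.7. The sample size itself is not in error: 25 per group reproduces at 2.5% two-sided with an assumed 80% power.

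The consequence depends on what was meant. If 0.005 applies to the primary endpoint, power falls from about 83% to 63% (two-sided t test, d = 0.95, 24 evaluable per arm), or from 90% to 72% if one-sided; 80% power two-sided would need 32 rather than 23 evaluable per arm. If 0.05 was meant, power is about 90% and the family-wise error can reach 10% instead of 5%. Neither reading agrees with the design. These figures rest on the assumed sidedness and on a t test; section 5.7 also allows Mann–Whitney U, for which power would differ.

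**What to change.** In section 5.7, state that each of the two primary questionnaires is tested two-sided at 0.025 (Bonferroni), with matching 97.5% confidence intervals, and correct or remove the 0.005. If the sentence was meant only for baseline comparability, say so. In section 5.3, state the sidedness and the power that this gives: about 83% for a t test with 24 evaluable per arm. Carry the same level into the statistical analysis plan.

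Plain Bonferroni keeps test and interval in agreement. A Holm procedure with 97.5% intervals would not, because its second step tests at 0.05.

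The cost is a change of wording in the protocol and the statistical analysis plan, with no extra patients. It applies the split over two questionnaires that section 5.3 has already adopted.
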